**Methods::**

We will conduct a longitudinal baseline study including quantitative measurement of key enteric pathogens and fecal indicator bacteria adjacent to households lacking adequate sanitation. As households connect to a new sewerage system serving the entire community, longitudinal household sampling will continue until crossover is complete. We will include concurrent comparison sites with existing appropriate sanitation as well as sites never receiving the intervention to monitor secular trends in pathogen releases during the study period.

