### Research Objectives and Hypotheses

The evaluation team will examine the effects of the infrastructure project on environmental contamination, infection risk, and individual well-being. These elements are addressed in the following primary (Objective 1) and secondary (Objectives 2–4) research objectives:
Objective 1: Measure the density of fecal microbes (enteric pathogens and fecal indicators) released to the local environment at the household and community levels before and after the implementation of a community-wide sanitation system. Hypothesis: Community-wide sanitation will result in a reduction in the density of enteric pathogens and fecal indicators in the environment.Objective 2: Collect qualitative and quantitative data regarding the type and functionality of pre- and post-intervention sanitation infrastructure at the household level through participant-taken and observational surveys. Hypothesis: The community-wide sanitation system will result in a reduction in the prevalence of failing sanitation systems and straight-pipe discharge sites.Objective 3: Model the effects of the implementation of a community-wide sanitation system on the enteric infection risks associated with exposure to enteric pathogens and fecal indicators. Hypothesis: Community-wide sanitation will reduce infection risks associated with exposure to enteric pathogens and fecal indicators.Objective 4: Explore whether and how the changes in sanitation service affect the quality of life of the participants included in the study. Hypothesis: The intervention will improve the quality of life for participants.

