### Data Analysis and Outcomes

Our primary outcome is to compare the concentration of culturable *E. coli* in the environment pre- and post-intervention using a time series regression analysis suitable for an interrupted time series ITS design. We will use the Durbin-Watson statistic to test the presence of autocorrelation in *E. coli* concentrations over time and will adjust for autocorrelation if found (29). To determine regression estimates that express the level (the average value of *E. coli* concentration at a given time point) and trend (the direction and rate of change in *E. coli* concentrations over time) of the outcomes pre- and post-intervention, we will use the generalized least-squares method with the Prais-Winston estimator (29). Regression coefficients corresponding to standard effect sizes on culturable *E. coli* soil concentrations will be obtained for a step change and a change in trend pre- and post-intervention. A step change, also known as a change in level, is the difference between the observed level at the first intervention time point and the predicted time trend. A change in trend is defined as the difference between the post-intervention and pre-intervention slopes, where slopes are defined as the rate of change in *E. coli* concentration over time (30).

Our secondary outcomes are the estimated prevalence of individual pre-specified pathogens in soil, wastewater, and surface water samples. We will graph the mean and standard deviation scores (the average measured values) for fecal markers and composite measurement, which summarizes the presence or concentration of multiple enteric pathogens within a sample. Within each sample type, only markers and composite indicators appearing in at least 10% of the samples collected at each time point will be included, in order to visualize the trends in fecal indicator concentrations and pathogen prevalence.

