### Quantitative Microbial Risk Assessment Model

We will use a quantitative microbial risk assessment (QMRA) model to compare the annual risk of enteric infection between pre- and post-intervention settings. QMRA is a probabilistic modeling approach that combines pathogen-specific dose-response models and population-specific exposure assessments to characterize the risk of infection from microbial hazards (31–34).

We will estimate the risk of enteric infection under pre- and post-intervention settings using the data collected in Objective 1. From this dataset, we will use measures of prevalence of enteric pathogens and concentrations of pathogen gene targets to estimate a distribution of pathogens in soil under both pre- and post-intervention settings.

We will estimate the viability of the enteric pathogens using a ratio of culturable *E. coli* to gene copies of *E. coli* recovered from the environmental samples. Using the ingestion parameters for soil from the US EPA exposure factors handbook, we will estimate a daily exposure dose of viable enteric pathogens. Using published dose-response models, we will then estimate a daily and annual risk of infection for pathogens that are in more than 10% of the samples. We will use stochastic methods to propagate variability and uncertainty throughout the model (35). We will then use previously described methods to generate effect measures estimating attributable reductions in risk of infection between pre- and post-intervention settings (36). The outcome for objective 3 is a modeled estimate of the change in daily and annual risk of enteric infection due to environmental exposure through soil by comparing pre- and post-intervention soil conditions.

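### Objective 1 concerns pathogen density, but the only outcome named for individual pathogens is prevalence, which responds weakly for frequently detected targets

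*Protocol article*

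**What the plan says.** The Research Objectives and Hypotheses section frames Objective 1, the primary objective, as: "Measure the density of fecal microbes (enteric pathogens and fecal indicators) released to the local environment at the household and community levels". Its hypothesis is: "Community-wide sanitation will result in a reduction in the density of enteric pathogens and fecal indicators in the environment". The Abstract (Methods) promises "quantitative measurement of key enteric pathogens and fecal indicator bacteria adjacent to households lacking adequate sanitation". The Methods and the Objective 1 overview send soil, wastewater and surface water for quantitative PCR on a custom array card.

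The Data Analysis and Outcomes section sets the primary outcome as a regression to "compare the concentration of culturable *E. coli* in the environment pre- and post-intervention". For pathogens it says: "Our secondary outcomes are the estimated prevalence of individual pre-specified pathogens in soil, wastewater, and surface water samples". It also plans graphs of means and SDs for fecal markers and for a "composite measurement, which summarizes the presence or concentration of multiple enteric pathogens within a sample". The stated purpose of the 10% inclusion rule for those graphs is "in order to visualize the trends in fecal indicator concentrations and pathogen prevalence".

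Pathogen quantity appears in one other analysis, the Objective 3 risk model, where "we will use measures of prevalence of enteric pathogens and concentrations of pathogen gene targets" to describe pathogens in soil before and after the intervention.

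**The concern.** The objective is about how much pathogen is present. The named pathogen outcome is about whether any is detected. The indicator half of the hypothesis has a density outcome (culturable E. coli), and the pathogen half has none. This is not a detail left for a statistical analysis plan: the protocol itself names the outcome, and the closing sentence of the same section repeats the split between indicator concentrations and pathogen prevalence.

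The choice matters most where a target is found in nearly every sample. There a substantial fall in concentration leaves most samples still positive, so the prevalence comparison has little room to show it. A rise in concentration among samples that are already positive would be hard to see for the same reason. The quantities needed to avoid this are already produced by the assay.

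**Working it through.** **The plan's own figure.** With total variance 5.2, within-household variance 4.3, ρ₁ = 0.16, d = 0.45, t = 6, two-sided 5% and 80% power, Equation 1 gives m = 2(1.960 + 0.842)² × 5.2 × 0.84 / (6 × 4.3 × 0.45²) = 13.1. Equation 2 as printed, with ρ₂ = 0.17 and k = 3, gives n = 13 × (1.17 × 2) = 30.4. Both match the stated 13 and 30. They concern soil E. coli; no sample size or power is stated for the pathogen outcome.

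**Inputs for the illustration.** The documents give no pathogen SD, detection limit or detection rate, so these are assumptions. Log concentration is taken as normal with mean M log above the detection limit. The main SD is √5.2 = 2.28, from pilot soil E. coli ybbW (Sample Size Calculations). SDs of 1.0 and 1.5 are shown as a range.

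**Response of prevalence.** Prevalence before is Φ(M/SD); after a fall of f log it is Φ((M − f)/SD). For M = 4 and f = 1: Φ(4/2.28) = Φ(1.75) = 96.0%, and Φ(3/2.28) = Φ(1.32) = 90.6%.

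| M | 1-log fall, SD 1.0 | 1-log fall, SD 1.5 | 1-log fall, SD 2.28 | 0.45-log fall, SD 2.28 |
|---|---|---|---|---|
| 4 | about 100% → 99.9% | 99.6% → 97.7% | 96.0% → 90.6% | 96% → 94% |
| 3 | 99.9% → 97.7% | 97.7% → 90.9% | 90.6% → 81.0% | 91% → 87% |
| 2 | 97.7% → 84.1% | 90.9% → 74.8% | 81.0% → 66.9% | 81% → 75% |

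At the sparse end with SD 2.28, a 1-log fall moves prevalence from 50% to 33% (M = 0) and from 33% to 19% (M = −1), so prevalence responds well there.

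**Information kept.** Let p be prevalence, a = Φ⁻¹(p) and φ the normal density at a. In units of 1/SD², detection alone carries φ²/(p(1 − p)) about the mean. A left-censored analysis of the same values, SD known, carries p − aφ + φ²/(1 − p). At p = 0.9, a = 1.282 and φ = 0.1755, so the two are 0.342 and 0.983, a ratio of 35%.

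| Prevalence | Information kept by prevalence |
|---|---|
| 10% | 95% |
| 20% | 92% |
| 50% | 78% |
| 80% | 51% |
| 90% | 35% |
| 95% | about 22% |

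**Power, for scale only.** Take 90 samples before and 90 after, treated as independent (an assumed 30 households × 3 visits), and a 1-log fall with SD 2.28. As M goes from 2 to 5, a prevalence comparison has power 57% down to 18%. A comparison of mean log concentration has Φ(1/(2.28 × √(2/90)) − 1.96) = 84%. With SD 1.0 the figures are 89% down to 3%, against more than 99%. The concentration figures treat every value as quantified, which flatters them somewhat at M = 2.

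**The case against.** The strongest reply is that density is not ignored. Objective 3 carries soil pathogen concentrations into a modelled before-and-after infection risk, for pathogens in more than 10% of samples. That includes the frequently detected targets, and a 1-log fall in one of them would lower its modelled dose and risk. The graphed composite may also use concentration. This stands as far as it goes. But the risk model covers soil only and reports risk. The composite pools pathogens, leaves open whether it uses presence or concentration, and is only graphed. Neither compares the density of a pathogen before and after.

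A reader might infer that the pathogen half of the hypothesis is untested, or that the trial would report no effect on pathogens despite a tenfold fall. The documents do not support that. Under the model used here prevalence falls whenever the mean falls, so comparing it still addresses the direction of the hypothesis, with less power where detection is common.

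The illustration also depends on unknowns. The SD is not that of any pathogen, and the detection margins are assumed. The protocol's 10% thresholds suggest that some targets are expected to be rare, and for those prevalence is a reasonable measure. Treating the SD as known favours the censored comparator.

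Wastewater is a poor example for the argument. The Wastewater Sample Collection section ties the sampling point to the household's current sanitation and uses system influent for households on the municipal system. It is therefore not a like-for-like series across connection, and log copies alone would not make it one.

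**Conclusion.** The mismatch between objective and outcome is stated in the protocol and stands. Its consequence is lost sensitivity for frequently detected targets. With SD 2.28, a 1-log fall shifts prevalence by about 14 points when the mean is 2 log above detection and by about 5 points when it is 4 log above. Prevalence keeps roughly half the information at 80% detection, about a third at 90% and under a quarter at 95%. At 10% to 20% detection it keeps over 90%. How many targets fall in the costly range cannot be told from the documents. The primary E. coli outcome and its sample size are unaffected, so this is a worthwhile correction to a secondary outcome and does not threaten the main analysis.

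**What to change.** In Data Analysis and Outcomes, add a pathogen outcome beside prevalence: the change in log gene copies per gram (soil) or per mL (surface water) for each pre-specified target detected often enough to quantify. Fix that threshold in advance, and treat non-detects as left-censored at the target's detection limit. Keep prevalence for all targets, and as the measure for those rarely detected. Apply the before-and-after contrast to soil and surface water. Report wastewater as a description of loading, because its sampling point changes on connection.

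The cost is a censored-data model and a documented detection limit for each target. No further samples or assays are needed, since the quantitative PCR values already exist for the planned work.

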### Sample Size Calculations

We calculated a sample size for our primary outcome using a time series regression appropriate for an ITS design. Here we calculate the number of households, *n*, that will be followed longitudinally across the six sampling time points, *t*, (three before and three after the intervention) to detect a meaningful change in soil *E. coli* concentrations with 80% power at a 5% significance level. Equation 1 calculates the crude number of households, *m*, needed before accounting for clustering (27).

Equation 1
$$m=\frac{2{\left(z_{\alpha }+z_{Q}\right)}^{2}\sigma^{2}\left(1-\rho_{1}\right)}{ts_{x}^{2}d^{2}}$$

In this equation the term *σ*^*2*^ captures the total variability in *E. coli* concentrations across all locations and time points, while *s*
^*2*^ accounts for the variability in repeated measurements within the same location. The intraclass correlation coefficient, ρ_1_ reflects how similar those repeated measures are over time for a given household. Finally, the effect size, *d*, is the expected change in log-transformed *E. coli* concentrations in soil attributable to the sanitation intervention.

To estimate the values used in this calculation, we used log-transformed concentrations of *E. coli* ybbW in soil samples based on preliminary data from soil samples collected in Hale County in 2023 (22). For sample size calculations, we assumed that *E. coli* ybbW in soil could serve as a proxy for culturable *E. coli* in soil, based on a moderate positive correlation observed between the two measures in soil samples (Spearman’s ρ = 0.54, *p* = 0.03). The total variance, *σ*^*2*^, was calculated as 5.2 log (copies/gram)^2^ based on all available soil samples. The within-household variance, *s*
^*2*^, was estimated as 4.3 log (copies/gram)^2^ from a mixed-effects model including a random intercept for location. The intraclass correlation coefficient, *ρ*_1_, which reflects the correlation of repeated measurements within a single location over time, was estimated to be 0.16. The effect size, *d*, was defined as a 0.45-log (copies/gram) reduction in soil concentrations, which corresponds to 20% of the standard deviation of log-transformed values from the pilot data. We selected this threshold to reflect a small but meaningful reduction in environmental fecal contamination. Using these inputs and *t* = 6 time points per household, we calculated an intermediate value of *m* = 13 households needed before adjusting for clustering.

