### Overview of the Study Design

We are collecting longitudinal microbial density data from environmental and household samples to estimate the reduction of pathogens and fecal markers released into the environment following the expansion of the wastewater treatment intervention. From the 50 recruited households, we will collect soil, wastewater, and drinking water samples to analyze for fecal indicators and enteric pathogens. We will conduct longitudinal surface water sampling from the receiving waters upstream and downstream of the discharge point of the new wastewater treatment system. All community members—both participants and non-participants—will be made aware that community-level sampling will be taking place for the purposes of this study at the community meetings described previously.

We will culture fecal indicator bacteria (total coliforms and *E. coli*) from environmental and household samples (wastewater, soil, drinking water, and surface water) using the IDEXX Colilert-18 Quanti-Tray 2000 System as independent predictors of exposure risk, to develop pathogen:indicator ratios for use in risk modeling, and as proxy indicators of pathogen viability in samples. We will further analyze the soil, wastewater, and surface water samples for pre-specified pathogens and fecal markers by real-time quantitative PCR (qPCR) using a custom TaqMan Array Card (28). Targets are specified in Appendix 1. We will use the microbial data collected before and after connection to the intervention to inform an interrupted time series (ITS) analysis. We are particularly interested in assessing the impact of the intervention on pathogens in the environment through drinking water, surface water, and soil sampling as proximal, objective, quantitative measures on the causal pathway from the intervention to all downstream health and non-health effects of improved sanitation services.

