### Soil Sample Collection

At each of the six time points, three soil samples will be collected from an area thought to be impacted by failing sanitation, as identified by the participant living in the household. If the household is relying on a cesspool or straight pipe, a sample will be collected directly at the point of impact by collecting the top layer of the receiving soil, with additional samples collected one foot away and three feet away from the point of impact. If the household is relying on a septic tank with a septic field, soil samples will be collected from three randomly selected locations overlaying the septic field. Impacted soil samples will not be collected at the 10 households with existing adequate sanitation services, which, by definition, have no directly impacted soils. As a control, three additional soil samples will be collected at all 50 households during each of the six sampling time points in a section of the yard that is identified by the participant as unimpacted by failing sanitation. If no such area exists, then the researcher will randomly sample at three locations at the front, side, and back of the home. Once initially selected, the same household soil locations will be sampled at each of the six time points.

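### The 10% detection rule for the marker and pathogen trend displays also uses the post-intervention time points, so targets that fall below 10% tend to drop out of view; the risk model's 10% rule does not say which samples count

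*Protocol article*

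**What the plan says.** The protocol article, Data Analysis and Outcomes (Objective 1), defines the secondary outcomes without any threshold: "Our secondary outcomes are the estimated prevalence of individual pre-specified pathogens in soil, wastewater, and surface water samples". It then plans graphs of fecal markers and a composite measure. For these, within each sample type, "only markers and composite indicators appearing in at least 10% of the samples collected at each time point will be included", and the stated purpose is "in order to visualize the trends in fecal indicator concentrations and pathogen prevalence".

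Sample Size Calculations fixes six time points, "three before and three after the intervention". The hypothesis for Objective 1 is a fall: "Community-wide sanitation will result in a reduction in the density of enteric pathogens and fecal indicators in the environment".

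Objective 3, Quantitative Microbial Risk Assessment Model, has a separate rule. Daily and annual risk will be estimated for "infection for pathogens that are in more than 10% of the samples". It carries no time-point condition and does not say whether the samples are pre-intervention, post-intervention or both.

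**The concern.** A rule that decides which targets are shown should not depend on the result being shown. Here a target must reach 10% at the three post-intervention points as well as the three earlier ones. One that is common at baseline and nearly eliminated after connection fails. One that the intervention leaves alone passes. The trend figures would then be weighted towards targets with little change, against the study's own hypothesis.

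In Objective 3 the issue is an undefined denominator. That rule is not about graphs: it decides which pathogens enter the modelled change in infection risk. If the denominator is chosen once data are in hand, the set of pathogens behind the Objective 3 result can change with that choice.

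**Working it through.** The article derives no figure from either rule, so there is nothing to reproduce. What follows illustrates how the rules behave.

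**Inputs from the protocol article**
- Six time points, three before and three after (Sample Size Calculations).
- 50 households (Overview of the Study Design). 20 are comparison households (Interrupted Time Series), which leaves 30 intervention households.
- Impacted soil: at each time point "three soil samples will be collected from an area thought to be impacted by failing sanitation", except at the 10 households with adequate sanitation (Soil Sample Collection). That gives 30 × 3 = 90 samples per time point from intervention households, or 40 × 3 = 120 with the 10 never-connected households that have poor sanitation.

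**Assumptions.** The article gives no pathogen prevalences, so all those below are assumed. Samples are first treated as independent, within and between time points.

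**Trend rule, intervention households only (n = 90, at least 9 positives needed)**

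P(kept) = P(Bin(90, p_pre) ≥ 9)³ × P(Bin(90, p_post) ≥ 9)³

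The single-time-point tail probabilities are 0.9965 at 20%, 0.551 at 10% and 0.036 at 5%, and about 1 at 30%.

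| Before → after | P(kept), all six points | P(kept), three earlier points only |
|---|---|---|
| 20% → 20% | 0.9965⁶ = 0.98 | 0.99 |
| 20% → 10% | 0.9965³ × 0.551³ = 0.17 | 0.99 |
| 20% → 5% | 0.9965³ × 0.036³ < 0.001 | 0.99 |
| 30% → 5% | < 0.001 | 1.00 |
| 50% → 12.5% | 0.53 | 1.00 |
| 50% → 25% | 1.00 | 1.00 |

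The last column shows that the loss comes from the post-intervention condition and not from the 10% level as such.

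**Never-connected households pooled in (n = 120, at least 12 positives needed).** The 30 samples from never-connected households stay at the baseline prevalence. P(kept) is 0.99 for 20% → 20%, 0.58 for 20% → 10%, about 0.045 for 20% → 5%, 0.38 for 30% → 5% and 0.98 for 50% → 5%. The loss is softer, and for very common targets it nearly vanishes.

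**Correlation within household.** Take a correlation of 0.17 between the three samples of a household (an assumption that borrows the value of ρ₂ in Sample Size Calculations) with a beta-binomial count per household and n = 90. P(kept) is then 0.94 for 20% → 20%, 0.15 for 20% → 10% and below 0.001 for 20% → 5%. Independence within a household does not drive the result.

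**The other reading of the wording.** If a target is left out only at the time points where it is below 10%, the post-intervention points of a target that was removed are blank, and the fall is still not shown.

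**Risk-model rule, pooled over equal pre and post numbers.** Pooled prevalence = (p_pre + p_post) / 2.
- 15% → 3%: (15 + 3) / 2 = 9%, excluded.
- 30% → 5%: (30 + 5) / 2 = 17.5%, kept.
- Any p_pre above 20% gives more than 10% even with p_post = 0, so it is kept.

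Only pathogens at or below 20% at baseline can be lost under this reading. If only pre-intervention samples count, the 15% → 3% pathogen is kept. The wording allows either.

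**The case against.** The strongest reply is that the trend rule governs a display. Its sentence ends with a purpose clause about visualizing trends and follows a sentence about graphs, while the secondary outcome is stated separately with no threshold. This stands. A reader might infer that targets failing the rule vanish from the results altogether, but the article does not say that their prevalence goes unestimated or unreported. What remains is that the trends to be displayed include pathogen prevalence, which is the secondary outcome, and a display that tends to omit the largest falls misleads in itself.

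A reader might also infer that the rule removes exactly the pathogens that the intervention removes. It does not. It also drops targets rare at baseline, and it keeps large falls that stay above 10%, such as 50% to 25%.

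On the risk model, two stronger readings are tempting. One is that large reductions in general would be dropped; the pooled arithmetic shows that this is confined to pathogens at or below 20% at baseline. The other is that a pathogen slipping just under 10% after connection would be credited with zero risk; the article says nothing about filtering each setting separately or setting excluded pathogens to zero.

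Finally, the size depends on assumed prevalences and on which samples form the denominator. This also stands: the softer figures with 120 samples are as consistent with the text as the harsher ones with 90. Wastewater and surface water were not examined.

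**Conclusion.** The point holds as a badly fixed selection rule for the secondary displays, together with an undefined denominator in the risk model. Followed as written, the trend rule makes inclusion depend on post-intervention prevalence, and the displayed trends tend to understate reductions. For a fall from 20% to 5%, the chance of being shown is below 0.001 with intervention households alone and about 0.045 with never-connected households pooled in, against 0.98 to 0.99 for a target unchanged at 20%. For 30% to 5% the corresponding figures are below 0.001 and 0.38. These rest on assumed prevalences, on three time points each side, on impacted soil only and on independence between time points.

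The primary analysis of culturable E. coli in soil is not touched, and nothing in the text suppresses the prevalence estimates. The matter is worth correcting before post-connection data are examined, but it does not threaten the main conclusion of the study.

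**What to change.** In Data Analysis and Outcomes, replace the condition at each time point with this: within each sample type, include a target if it is found in at least 10% of the pooled pre-connection samples or at least 10% of the pooled post-connection samples; hold that single list fixed for every time point; and report prevalence for every pre-specified target whether or not it is plotted.

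The list should draw on either period and not on the pre-connection period alone. Treated effluent will be discharged to a local creek, and a baseline-only list would hide a pathogen that is rare there before discharge and common afterwards. Treatment-system influent and effluent are sampled only after connection, so those sample types must use their own post-connection samples.

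In Quantitative Microbial Risk Assessment Model, state which samples the 10% refers to and use one common list, built in the same way, for both the pre- and post-intervention settings.

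The cost is a sentence or two in each of the two places and no new sampling. Some plots will show sparse markers.
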